## Abstract

**Background::**

Contingency management (CM) is an intervention for alcohol use disorder (AUD) that reinforces abstinence, as confirmed by alcohol biomarkers. CM is usually brief (12–16 weeks) despite evidence that longer interventions have better long-term outcomes. Most CM models are in-person which can also be a barrier for treatment. Studies of longer duration telehealth-based CM models are needed.

**Aims::**

To determine if a telehealth-based CM model that utilizes phosphatidylethanol (PEth) to confirm abstinence is effective at reducing alcohol use during a 26-week intervention and 12-month follow-up. We will evaluate the impact of CM on alcohol-related outcomes, determine if Addiction Neuroclinical Assessment variables are associated with outcomes in follow-up, and whether savings related to decreased alcohol use offset intervention costs.

**Methods::**

Adults with AUD residing in the United States will be recruited via online advertising. Research procedures will be conducted virtually. Participants who submit a PEth-positive blood sample (≥20 ng/mL) at enrollment will be randomized to 26 weeks of either 1) online cognitive behavior therapy (CBT4CBT) with rewards not contingent on PEth results (Control group) or 2) CBT4CBT with a maximum of $1,820 of rewards contingent on PEth results (CM group). Efficacy outcomes of PEth-negative tests (primary) and PEth-defined excessive drinking (≥200 ng/mL; secondary) will be assessed. Predictors of intervention outcomes and economic viability will also be investigated.

**Discussion::**

If this telehealth-delivered PEth-based CM intervention reduces alcohol use and is cost-effective, it could be used to provide effective treatment to millions of individuals with AUD who do not receive in-person care.

## Introduction

1.

Despite the availability of treatment options for alcohol use disorder (AUD), few individuals with AUD seek treatment [1]. Poor treatment utilization may result from barriers associated with in-person care, e.g., inconvenience, transportation costs, stigma [2]. During the COVID-19 pandemic, 60% of substance use disorder patients received some portion of their substance-related treatment via telehealth [3]. Prior to the pandemic, virtual treatments were also evaluated and disseminated as treatment options for patients with substance use disorders. These included online cognitive behavioral therapies, such as Computer Based Training for Cognitive Behavioral Therapy (CBT4CBT) and telehealth-based contingency management (CM) [4,5]. However, this work has focused on telehealth treatment for illicit drug use, while telehealth treatments for AUD are limited to pilot studies [6,7]. Telehealth interventions have potential limitations (e.g., access to and comfort with technology), however its advantages likely outweigh disadvantages for individuals with AUD who do not or cannot access in-person care. Randomized controlled studies evaluating the efficacy of telehealth-based treatment models for AUD are needed.

CM is ideal for telehealth delivery given its simple procedural nature, which consists of individuals receiving tangible reinforcers in exchange for meeting treatment goals (e.g., reducing substance use, maintaining abstinence). Initial telehealth and app-based CM models indicate reductions in drug and alcohol use (e.g., DynamiCare, FDA-approved reSET) [6–12,23,26,27]. For AUD, these telehealth-based CM models have utilized transdermal monitors or repeated daily breath sampling, which can be costly, burdensome, and stigmatizing for patients [6,7,9,11]. Another factor that can impact the efficacy of a telehealth-based CM model is the intervention duration. A meta-analysis found that CM was associated with a 22% higher odds of post-treatment illicit drug abstinence in comparison to other interventions, and that the best predictor of long-term abstinence was the length of the CM intervention [33]. The utilization of alcohol biomarkers that have a longer window of detection is one method to extend telehealth-based CM duration while also reducing burden on patients through decreased sampling and visit frequency.

We previously conducted a pilot study for a telehealth-based CM model that used the blood biomarker phosphatidylethanol (PEth) to assess alcohol consumption [7]. The PEth homologue 16:0/18:1 can be detected for up to 28 days [8], thus assessing abstinence or low levels of drinking can occur as infrequently as once a month. Accordingly, our pilot study (*n* = 16) used a two-phase CM treatment approach. Phase 1 helped participants initiate abstinence with weekly PEth assessment and reinforcement of week-to-week decreases in PEth levels. Once PEth levels indicated sustained reductions in alcohol consumption (PEth <20 ng/mL), participants transitioned to Phase 2 where sampling and reinforcement decreased to once every two to four weeks. By reducing sample frequency, we were able to extend the CM intervention duration to 26 weeks. Participants reported high satisfaction with study procedures, to include self-collection of blood samples using the TASSO-M20 device, suggesting that our telehealth-based model was feasible. Additionally, CM participants were five times more likely than Control participants to submit PEth samples indicative of alcohol abstinence (*p* = 0.007), indicating that our telehealth-based CM model was also efficacious [7].

Based on these pilot results, we received funding to conduct a randomized controlled clinical trial of our telehealth-based CM intervention for AUD (R01AA031013; ClinicalTrials.gov ID NCT06265506). For this study, our primary aim is to determine whether the frequency of PEth-defined abstinence (<20 ng/mL) or absence of regular excessive drinking (<200 ng/mL) is higher in those receiving CM compared to the Control group during the intervention and follow-up periods. Additional aims include a) assessing group differences in alcohol-associated harms, (e.g., cigarette/tobacco use, drug use, costly medical care), b) describing the association between the Addictions Neuroclinical Assessment (ANA) framework variables (incentive salience, executive functioning, negative emotions) and alcohol outcomes [9], and c) conducting a cost-effectiveness analysis to determine the value of the CM group relative to the Control group, from the healthcare sector, state policymaker, and societal perspectives.

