### Preliminary analyses

3.1.

Our data and supporting documents will be submitted to the National Institute on Alcohol Abuse and Alcoholism’s National Data Archive (NDA) and will be available within three years of completion of the study. Groups will be compared for differences in demographics and pre-treatment alcohol use. Means and standard deviations will characterize continuous variables, and percentages and frequencies characterize categorical variables. We will assess the impact of sex as a biological variable. Our alpha threshold for statistical significance will be 0.05.

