### Treatment efficacy

3.2.

We will follow an intention-to-treat approach to provide unbiased group comparisons. Treatment efficacy will be assessed per our primary outcome, PEth-defined abstinence. In the Starting Phase, abstinence will be defined as a week-over-week decrease in PEth levels (yes/no). During the Sustaining Phase and Follow-up Phase, abstinence will be defined as PEth <20 ng/mL (yes/no). Separate generalized estimating equations (GEE) with logit link functions will be used to assess abstinence during treatment (11 assessments across 26 weeks) and follow-up (4 assessments across 52 weeks). The frequency of PEth-defined excessive drinking (≥200 ng/mL; yes/no) will also be analyzed with GEE. GEEs with appropriate link functions will also assess additional outcomes for the longest duration of PEth-defined abstinence, uEtG results (positive/negative), self-reported days of drinking, self-reported drinks per day, and alcohol-associated harms (cigarette smoking, drug use, utilization of costly medical care). All GEE models will include effects for groups, biological sex, time, and the group-by-time interaction. Statistically significant group-by-time interactions will be evaluated with Bonferroni corrected post hoc tests.

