### Power

3.5.

Our sample size (*n* = 200) is based on statistical power calculations with the primary outcome of detecting group differences in PEth-assessed alcohol abstinence across 11 assessments during treatment and 4 assessments in follow-up. Our missing data techniques will recapture some power lost due to attrition, but we take a conservative approach to ensure adequate power by basing power calculations on a sample size reduced by 25% (*n* = 150). Our pilot study found an increase in abstinence of 43% in the CM group compared to 0% in the Control group. Using methods previously described [45], this effect would result in >99% power with *n* = 150 when comparing abstinence among groups in treatment (G*Power software). While this effect is promising, CM meta-analyses and large RCTs consistently demonstrate odds ratios (ORs) as effect sizes ranging from 1.7 to 4.5 for increasing substance use abstinence [23,46–51]. In addition, CBT4CBT, which all participants will receive, has an effect size on substance use ranging from *d* = 0.11–0.37. These are modest and consistent with CBT interventions that are commonly paired with CM in past trials where CM demonstrated superiority to CBT [47,49,52]. Based on our pilot study, we expect an effect size no smaller than OR = 1.7, which accounts for the underlying effect of CBT in both groups. In the treatment and follow-up period, at a sample size of *n* = 150, we will have at least 80% power to detect a modest effect size of OR = 1.34.

For the secondary aim of reducing the frequency of PEth-defined excessive drinking, our group has consistently found secondary improvements in the odds of substance-related harms to be OR = 1.80 or larger. Assuming a sample size of n = 150, we estimate at least 80% power to detect an OR = 1.80 for reduction in PEth-defined excessive drinking during treatment or the follow-up period.

For analyses of the ANA, our proposed sample size of n = 150 will provide at least 80% power to identify an OR = 1.44 when there are as many as 10 predictors being modeled. This OR corresponds to a small but clinically meaningful change predicted by demographics, our ANA variables, and in-treatment PEth-defined abstinence.

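### The article disagrees with itself on whether excessive drinking is primary, and its primary abstinence outcome is tested in two periods at an unsplit 0.05 with no decision rule

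*Protocol article*

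**What the plan says.** **Which outcome is primary.** The Introduction (final paragraph) joins two outcomes in the primary aim: "PEth-defined abstinence (<20 ng/mL) or absence of regular excessive drinking (<200 ng/mL) is higher in those receiving CM compared to the Control group". The additional aims listed after it do not mention excessive drinking, so in that section it appears only inside the primary aim. Three other places differ:

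- Abstract, Methods: "Efficacy outcomes of PEth-negative tests (primary) and PEth-defined excessive drinking (≥200 ng/mL; secondary) will be assessed".
- 3.2 Treatment efficacy: "Treatment efficacy will be assessed per our primary outcome, PEth-defined abstinence".
- 3.5 Power: "For the secondary aim of reducing the frequency of PEth-defined excessive drinking", with its own detectable odds ratio.

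**Which period decides.** The Introduction's aim is that the frequency "is higher in those receiving CM compared to the Control group during the intervention and follow-up periods". Section 3.2 fits separate logit GEE models for treatment (11 assessments) and follow-up (4 assessments), and 3.5 bases the sample size on both.

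**Error control.** Section 3.1 says "Our alpha threshold for statistical significance will be 0.05". The only adjustment in the article is in 3.2: "Statistically significant group-by-time interactions will be evaluated with Bonferroni corrected post hoc tests".

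**The concern.** A reader of the final report needs to know which result makes the trial positive. On this text the answer depends on the section consulted. Under the Introduction, a benefit on the 200 ng/mL threshold alone could be presented as meeting the primary aim. Under the Abstract, 3.2 and 3.5 it could not.

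Settling that conflict in favour of abstinence still leaves two models, two p-values and one unsplit 0.05. If only one period is significant, the text does not say whether efficacy has been shown. The Bonferroni step applies after a significant interaction, within a model, and does not cover the choice between periods or outcomes. What is at stake is a false claim of efficacy at more than the stated 5%, and a dispute over interpretation if the periods disagree. The second outcome is plausible here, because section 4 itself calls the evidence for post-intervention effects of CM less conclusive.

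**Working it through.** **Inputs from the article.** Significance level 0.05 (3.1); two abstinence models (3.2); two outcomes joined in the primary aim (Introduction); n = 150 for power, pilot rates of 43% and 0%, expected OR 1.7 (3.5).

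**Assumed, because not stated.** Two-sided tests, 75 per arm, and the correlation between test statistics, which is shown as a range.

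**1. The plan's own figure.** Section 3.5 gives more than 99% power for 43% versus 0% in treatment. For a single two-proportion comparison at two-sided 0.05:
- null SE = √(2 × 0.215 × 0.785 / 75) = 0.0671
- alternative SE = √(0.43 × 0.57 / 75) = 0.0572
- z = (0.43 − 1.96 × 0.0671) / 0.0572 = 5.2, so power exceeds 99.99%

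The figure reproduces, and it does so as one comparison at the full 0.05.

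**2. The four places side by side.**

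| Place | Abstinence | Excessive drinking |
|---|---|---|
| Introduction | in primary aim | in primary aim |
| Abstract, Methods | primary | secondary |
| 3.2 | primary outcome | also analysed |
| 3.5 | primary outcome | secondary aim |

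Three of the four support abstinence as the only primary outcome.

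**3. Error with abstinence alone, success in either period.**
- Independent tests, two-sided: 1 − 0.95² = 9.75%
- Bivariate normal, correlation 0.5: 9.1%; correlation 0.8: 7.8%
- Favouring CM only, independent: 1 − 0.975² = 4.9%; correlation 0.8: 3.9%

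Null simulations of the GEE models gave 8.8% and 10.0% in two scenarios. Each used 3,000 trials with n = 150, 11 + 4 visits, terms for group, sex, time and group-by-time, and robust standard errors. The PEth variances and correlations were assumed, and abstinence was simplified to PEth <20 ng/mL at every visit. The correlation between the two abstinence tests came out at 0.72 and 0.36 respectively. Monte Carlo error is about √(0.09 × 0.91 / 3000) = 0.5 percentage points, so the results agree with the formulas.

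**4. Error under the literal Introduction, any of four comparisons.**
- Independent, two-sided: 1 − 0.95⁴ = 18.5%
- Common correlation 0.5: about 15.5%; 0.8: 11.4%
- GEE simulation: 15.9% and 17.1%
- Favouring CM only, independent: 1 − 0.975⁴ = 9.6%; simulation 8.3% and 9.1%

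**5. If both periods must succeed.** The chance that both abstinence tests are falsely significant cannot exceed 5%, so there is no inflation. The issue is that the rule is not stated.

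**6. What splitting alpha would cost.** Take OR 1.7, and assume a control rate of 30% and a within-person correlation of 0.3.
- CM rate = 0.729 / 1.729 = 0.421, where 0.729 = (0.3 / 0.7) × 1.7
- design effect = 1 + 10 × 0.3 = 4; effective observations per arm = 75 × 11 / 4 = 206
- SE of log OR = √[(1/0.210 + 1/0.244) / 206] = 0.207; z = 0.531 / 0.207 = 2.56
- power at 0.05: Φ(2.56 − 1.96) = 73%
- power at 0.025: Φ(2.56 − 2.24) = 62%

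This illustrates the cost of a split and is not an estimate of the trial's power.

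**The case against.** The strongest reply is that 3.2 is the operative section. It names abstinence alone, and the Abstract and 3.5 agree, so the Introduction is a loose summary. That is largely right about intent. It means a reader who infers that the trial can succeed by any of four routes is relying on one sentence that three other places overrule. The 11-18% range therefore describes the Introduction's wording and not the plan as a whole. The conflict in the published text remains, and a SAP would not remove it.

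Second, the Introduction speaks of intervention *and* follow-up, which could mean that both are required. That stands as a possible reading, and under it the error is not inflated. But no section says so.

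Third, a reader might infer from 3.2 that the group-by-time interaction is the test of efficacy, or that the group coefficient would be the effect at Week 1 only. The article supports neither. It lists the model terms and says how a significant interaction is followed up. It names no reference coding and does not make the interaction the efficacy test. Coding and contrasts may be set in the SAP. Nor can one say that little could differ at Week 1: in the Starting Phase the outcome is a week-over-week decrease in PEth, not a level below 20 ng/mL.

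Finally, the SAP may also name a decisive period. If it does, the article should carry the same statement.

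**Conclusion.** The concern holds in limited form. The contradiction is certain from the text: the Introduction makes absence of excessive drinking part of the primary aim, and the Abstract, 3.2 and 3.5 do not. With abstinence alone as primary, two periods share an unsplit 0.05 with no decision rule. If either period suffices, the two-sided error is about 8-10%, that is 1.6 to 2 times nominal (7.8/5 to 9.75/5). Counting only errors favouring CM it is about 4-5% against 2.5%. These figures assume two-sided tests, correlations between 0 and 0.8, and an either-period claim, which the article neither states nor excludes. The range of 11-18% applies only if the Introduction is taken literally. The inflation is moderate and removing it is cheap, so the change should be made before outcomes are compared by arm.

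**What to change.** 1. Reword the primary aim in the Introduction so that abstinence is the only primary outcome and excessive drinking is secondary, as in the Abstract, 3.2 and 3.5.
2. In 3.2, name one primary test: the group effect on PEth-defined abstinence in the treatment-period GEE, averaged over the scheduled visits, at two-sided 0.05. Keep the phase-dependent outcome definition already in 3.2. Replacing it with PEth <20 ng/mL at every visit would change the primary outcome and would have to be declared and justified as such.
3. Then test in fixed order, each at 0.05 and only if the one before succeeds: follow-up abstinence, treatment-period excessive drinking, follow-up excessive drinking.
4. Describe the group-by-time interaction as descriptive.

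**Cost.** The change is to the text. The first test keeps the full 0.05 and loses no power. A later comparison cannot be claimed once an earlier one fails, so a follow-up benefit without a treatment-period benefit would be exploratory. If the sponsor wants either period to count, 0.025 for each holds the error at 1 − 0.975² = 4.9%, at an illustrative fall in power from 73% to 62%. Requiring both periods also holds the error, but it lowers the chance of success and would have to be stated.

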## Methods

2.

### Study design

2.1.

We aim to randomize 200 adults with an AUD from the contiguous United States. Targeted internet advertisements will recruit participants. Advertisements will direct individuals to the study landing page to complete a screening survey and provide contact information. Those potentially eligible will be scheduled for an enrollment visit via a Health Insurance Portability and Accountability Act compliant Zoom. During enrollment, an electronic consent form and eligibility interview will be completed. Additionally, a blood sample for the assessment of PEth will be self-collected using the TASSO-M20 device, along with a self-collected urine sample to assess the alcohol biomarker urine ethyl glucuronide (uEtG). Participants will ship their blood samples via prepaid envelopes for laboratory assessment and conduct uEtG testing on camera with staff using a dipcard.

Participants whose PEth levels are ≥20 ng/mL, indicating alcohol use in the last four weeks, will be randomized to a 26-week intervention period of either: 1) CM group, in which participants complete online CBT4CBT modules and receive reinforcers that are contingent on PEth results, or 2) Control group, in which participants complete online CBT4CBT modules and receive reinforcers regardless of PEth results. After the intervention period, participants will complete follow-up assessments at Weeks 30, 38, 52, and 78 (i.e., 12-month duration) to determine the long-term effects of CM and predictors of abstinence (see Fig. 1). All study visits will occur via Zoom with reinforcers delivered as electronic gift cards using Tango (e-gift cards; tango.com) with restrictions on the purchase of alcohol, tobacco, and firearms.

### Study procedures

2.2.

#### Participant eligibility

2.2.1.

Inclusion criteria include: 1) two self-reported heavy drinking episodes (>4 standard drinks for male assigned at birth, >3 standard drinks for female assigned at birth) or ≥14 standard drinks in the last 14 days at the time of screening; 2) a PEth level that is ≥20 ng/mL at study enrollment; 3) diagnosis of a current AUD as assessed by the Structured Clinical Interview for DSM-5 (SCID) [10]; 4) 18+ years of age; 5) residing in the contiguous USA; 6) fluent in English; 7) access to reliable internet for videoconferencing. Ineligibility criteria include: 1) current SCID diagnosis of a severe drug use disorder, excluding cannabis; 2) receiving other AUD treatment at study enrollment; 3) inability to provide informed consent based on the San Diego Brief Assessment of Capacity to Consent; 4) history of alcohol withdrawal-related seizures or alcohol-related hospitalization in the prior 12 months; or 5) psychiatrically or medically unsafe to participate, per the principal investigator. Should a participant enroll in another AUD treatment after randomization, they will remain in the study.

#### Randomization procedures

2.2.2.

Eligible participants will be assigned to study arms based on permuted block randomization in REDCap that is stratified by sex (male, female, other, prefer not to say) and PEth levels at the study enrollment visit (<200 ng/mL or ≥200 ng/mL). PEth ≥200 ng/mL equates to regular excessive drinking in the prior two to four weeks [11,12]. Participants will be informed of their treatment condition at the randomization visit, one week after enrollment (see Fig. 1).

### Study interventions

2.3.

#### CBT4CBT

2.3.1.

All randomized participants will receive CBT4CBT, which is an evidence-based computerized intervention for substance use that was adapted and tested for AUD [4,13–19]. CBT4CBT teaches the principles of cognitive behavioral therapy (CBT) through video, graphics, audio instruction, interactive exercises, and homework [20]. Participants will complete six modules during the first eight weeks of treatment (~40 min/module). The program tracks how long participants are logged in, the modules completed, homework assignments completed, and to what degree CBT principles are learned through quizzes. Participant engagement will be monitored and supported by staff during study visits.

#### CM group

2.3.2.

Participants will receive CBT4CBT in addition to their reinforcers being contingent on PEth results. The criteria for PEth-verified abstinence will differ depending on the treatment phase. During the Starting Phase, week-over-week decreases in PEth levels, regardless of the amount, will be reinforced until participants reach PEth <20 ng/mL, which is consistent with approximately four weeks of abstinence. After completing 4 weeks of the Starting Phase and/or achieving PEth <20 ng/mL, participants will transition to the Sustaining Phase with visits every two to four weeks, as long as abstinence is maintained. Should PEth levels indicate that drinking occurred since the last visit (≥20 ng/mL), CM participants will return to the Starting Phase with weekly visits until PEth levels once again indicate abstinence (see Fig. 2). Returning to the Starting Phase provides CM participants with additional support when a drinking episode occurs. Participants will continue the Sustaining Phase when their PEth levels return to abstinence (<20 ng/mL), and treatment duration will remain 26 weeks regardless of how long a participant remains in the Starting Phase or how many times they return to the Starting Phase.

During the Starting Phase, participants will receive $20 for the first PEth result that indicates reduced alcohol consumption (i.e., week-to-week decrease). They will then receive an additional $5 for every week of consecutive abstinence (i.e., week-to-week decrease during the Starting Phase, <20 ng/mL during the Sustaining Phase). PEth-positive samples (i.e., week-to-week PEth increase, PEth ≥20 ng/mL) will result in reinforcers being withheld until the next negative test, for which the participant will earn $20. A subsequent negative test will then reinstate the total reinforcers earned prior to testing positive, plus an additional $5. For example, if a participant previously earned $40 but then tests positive, they will receive $0 at the current visit. When the participant submits the next negative sample, they will earn $20, and then be eligible for reinstating their highest earned total (e.g., $40) plus an additional $5 when they have two consecutively negative samples. This reinforcer escalation schedule, reset, recovery approach is consistent with previous CM studies [21,22].

If CM participants have an unexcused missed visit or do not ship their sample within a week of the study visit, the PEth sample will be considered positive. In such cases, reinforcers will be withheld, and the participant will return to the Starting Phase. The maximum CM reinforcer that can be earned per week of abstinence is $90 (e.g., for visits occurring once every 4 weeks the max is $360). The maximum total amount that can be earned for negative PEth results during the CM intervention is $1,820.

